## Abstract

**Background:**

Physical activity is essential to improve health and reduce the risk of recurrence of stroke or transient ischemic attack (TIA). Still, people post stroke or TIA are often physically inactive and the availability of physical activity promotion services are often limited. This study builds on an existing Australian telehealth-delivered programme (i-REBOUND– Let’s get moving) which provides support for home-based physical activity for people post stroke or TIA. The aim of this study is to test the feasibility, acceptability, and preliminary effects of a mobile Health (mHealth) version of the i-REBOUND programme for the promotion of physical activity in people post stroke or TIA living in Sweden.

**Methods:**

One hundred and twenty participants with stroke or TIA will be recruited via advertisement. A parallel-group feasibility randomised controlled trial design with a 1:1 allocation ratio to 1) i-REBOUND programme receiving physical exercise and support for sustained engagement in physical activity through behavioural change techniques, or 2) behavioural change techniques for physical activity. Both interventions will proceed for six months and be delivered digitally through a mobile app. The feasibility outcomes (i.e., reach, adherence, safety and fidelity) will be monitored throughout the study. Acceptability will be assessed using the Telehealth Usability Questionnaire and further explored through qualitative interviews with a subset of both study participants and the physiotherapists delivering the intervention. Clinical outcomes on preliminary effects of the intervention will include blood pressure, engagement in physical activity, self-perceived exercise self-efficacy, fatigue, depression, anxiety, stress and health-related quality of life and will be measured at baseline and at 3, 6 and 12 months after the baseline assessments.

**Discussion:**

We hypothesise that the mHealth delivery of the i-REBOUND programme will be feasible and acceptable in people post stroke/TIA living in rural and urban regions of Sweden. The results of this feasibility trial will inform the development of full-scale and appropriately powered trial to test the effects and costs of mHealth delivered physical activity for people after stroke or TIA.

**Trial registration:**

ClinicalTrials.gov Identifier: NCT05111951. Registered November 8, 2021.

## Background

Stroke is largely preventable yet it remains the second-leading cause of death globally and the third-leading cause of death and disability combined [1]. Rates of recurrent stroke or other cardiovascular events following a stroke are high [2, 3], with a cumulative risk of stroke recurrence of 26.4% at 5 years post stroke [2]. Furthermore, individuals who have undergone their first stroke or transient ischaemic attack (TIA) have a sixfold increase in the risk of a recurrent stroke, with secondary events resulting in greater mortality as well as often being both more disabling and costly [4, 5]. TIA is, in addition, a strong predictor of stroke [6] and an independent predictor of long-term mortality [4, 5]. While pharmacological management is crucial in secondary stroke prevention, non-pharmacological interventions focusing on lifestyle modifications (e.g., physical activity and diet) also play an important preventive role [3, 7].

People post stroke or TIA are prone to sedentary lifestyles as sedentary time has been shown to be proportional to increased age [8, 9], with most people experiencing a stroke or TIA at 65 years of age or older [10]. Previous studies have reported that people post stroke spend approximately 30% more time sitting [11] and take less than half the number of steps per day (4078 vs 8338 steps) [12], when compared to healthy individuals. Physical activity has been shown to improve cardiorespiratory fitness and decrease stroke related burdens such as fatigue, depression, and anxiety [13]. Engagement in moderate to vigorous physical activity has shown promising effects on cardiovascular health (e.g., blood pressure reduction) post stroke or TIA [7, 14] with a 40% risk reduction of stroke recurrence 3 years after stroke onset in those who are physically active [15].

Several existing challenges need to be addressed when developing interventions to promote engagement in physical activity post stroke or TIA. First, self-management strategies for physical activity alone have not been shown to increase physical activity post stroke or TIA [14, 16, 17]. Instead, studies have shown that combining supervised exercises with behaviour change techniques for physical activity for more than 4 months to be the most effective in increasing physical activity and improving cardiovascular health [7, 14]. Core behaviour change components of physical activity engagement post stroke or TIA include individual counselling [18], goal setting [19, 20], self-monitoring and structured follow-ups [20] in order to address known barriers for behaviour change. Such barriers are often related to self-efficacy (i.e. the belief a person has in his or her ability to perform a particular behaviour successfully and obtain the intended results) [21], health literacy, and adherence [22]. Second, whilst supervised exercise is often available to people post stroke or TIA, barriers such as rural living and a lack of transportation to facilities which are often located far away hinder access to such services [23].

In Sweden approximately 30,000 people experience a stroke or TIA annually, of which around 20% withstand a recurrent episode [10]. With a population density of 25 people/km^2^ [24] many individuals have limited access to healthcare services with a large variation in the type and availability of stroke rehabilitation observed [10]. One of the challenges for rehabilitation clinics is to provide support for physical activity, particularly for those living remotely [10]. This could be accomplished through mobile health (mHealth), i.e. medical and public health services supported by mobile devices (e.g. mobile phones, patient monitoring devices and applications) [25]; a promising avenue for providing equal and accessible health promotion services to people post stroke or TIA. Despite patients and healthcare professionals reporting high levels of acceptance towards mHealth both globally [26] and locally [27], implementation of mHealth services has been limited during the Covid-19 pandemic in Sweden [27]. mHealth can be beneficially adopted at various points during the patient-clinician therapeutic process from assessment, through to intervention, support, and follow-up [28, 29]. Current low-to-moderate level evidence suggests that remote services (such as mHealth) are no less effective than usual care post stroke with respect to activities of daily living [29, 30], health-related quality of life [29, 30] and depression [29–31]. Despite its potential, the feasibility and long-term effects of mHealth services for specifically promoting physical activity post stroke or TIA remain largely unknown [29, 30]. Furthermore, existing mHealth interventions for people post stroke or TIA use a hybrid approach combining one (or more) physical meetings with mHealth services [29, 30]. Few previous studies have evaluated a completely digital approach for promotion of physical activity (i.e., no physical visits) supported by mHealth post stroke or TIA. To make full use of the potential of mHealth services regarding reach and accessibility, the feasibility of a completely digital approach for promotion of physical activity post stroke or TIA needs to be explored.

This study is an extension to an existing telehealth-delivered programme (i-REBOUND– Let’s get moving) developed in Australia [32, 33] which provides support for home-based physical exercise and physical activity through behaviour change techniques to people post stroke or TIA via video meetings (i.e., “Zoom”). [34]. The overarching aim of this study is to test the feasibility, acceptability, and preliminary effects of this mHealth version of the i-REBOUND programme for promotion of physical activity in people post stroke or TIA living in Sweden. A logic model has been created to explicitly illustrate intervention theory with regard to resources, core intervention components, mechanisms of change, and expected outcomes of this trial, as shown in Fig. 1. Expected key mechanisms for change in long-term engagement in physical activity are strengthened physical functioning and self-efficacy, positive reinforcement of physical activity, increased awareness of the importance of physical activity for health as well as positive perceptions of engagement in the i-REBOUND programme (e.g., motivation, interest, and creation of routine for sustaining engagement in physical activity) [19].

**Fig. 1 Fig1:**
[figure not shown]
Logic model illustrating intervention theory regarding resources, core intervention components, mechanisms of change, and expected outcomes of this trial

Specific study objectives are:1. To assess the feasibility of the mHealth version of the i-REBOUND programme regarding reach, protocol and programme adherence, safety and fidelity.2. To explore how people post stroke or TIA experience supervised support for physical activity, and behaviour change support for sustaining engagement in physical activity, through the mHealth version of the i-REBOUND programme.3. To determine the acceptability of the mHealth version of the i-REBOUND programme with respect to mobile app usability and support provided for engaging in physical activity.4. To explore the preliminary effects of the mHealth version of the i-REBOUND programme, compared to the standard approach used in Sweden for general physical activity promotion, on physical activity, blood pressure, exercise self-efficacy, fatigue, depression, anxiety, stress, and health related quality of life.

## Methods

### Design

A prospective two-arm feasibility randomised controlled trial, with an embedded qualitative study, will be conducted in accordance with the CONSORT checklist for feasibility studies [35]. The trial flowchart and design are presented in Fig. 2. The trial is registered at ClinicalTrials.gov (NCT05111951, registered date: 08/11/2021) and has been approved by the Swedish Ethical Review Authority (dnr 2020–05,062, 2021–03,622 and 2022–04,042-02). Written informed consent will be obtained from participants prior to starting the data collection.

**Fig. 2 Fig2:**
[figure not shown]
Study flowchart

### Participants

One hundred and twenty adults diagnosed with a stroke or TIA will be recruited across rural and urban areas of Sweden through advertisements at outpatient clinics, the Karolinska Institutet homepage, patient organisations and social media. The inclusion of 120 study participants builds on our aim to test the feasibility of the mHealth version of the i-REBOUND programme among people post stroke or TIA situated both in urban and rural areas, with variation in disability, exercise habits, physical activity levels, age, gender and technology use. The sample size is in line with recommendations regarding feasibility studies [36].

Inclusion criterion are: (i) between 3 months and 10 years post stroke or TIA at point of study enrolment, (ii) living at home, (iii) with the ability to walk short distances indoors with or without a walking device, (iv) able to use a smartphone, (v) have access to a stable internet connection, and (vi) ability to digitally self-identify using BankID. BankID is a Swedish smartphone and computer application considered to be secure and used by authorities to log into e-services and sign contracts electronically.

Exclusion criterion are: (i) already meeting the recommended physical activity levels of at least 150 min per week of moderate physical activity or at least 75 min per week of vigorous intensity physical activity [37] assessed using the International Physical Activity Questionnaire [38], (ii) severe health conditions (e.g. cardiac conditions, other neurological diseases and severe arthritis), (iii) significant cognitive impairment, neglect or aphasia compromising engagement in the intervention, or iv) enrolled in a concomitant clinical trial or participating in rehabilitation (e.g. aerobic exercises) at the time point of recruitment.

### Study procedures

Study participants will access the respective experimental or control intervention via the STAAR app which is available for iPhone and Android smartphone users. The STAAR app is integrated with a digital clinic; a cloud-based portal accessible through any web browser, enabling therapist-patient communication through chat- and video calls and remote assessment through digital questionnaires. The digital clinic will be used by the physiotherapists delivering the experimental and control interventions, and by the research team to coordinate the trial and to collect data on feasibility, acceptability and clinical outcomes.

Screening for eligibility of study participants will be performed in two steps by members of the research team. First, interested participants will take part in a telephone interview to assess trial eligibility criteria related to stroke or TIA diagnosis, living conditions, ambulation status and mobile phone proficiency. Individuals meeting the inclusion criteria will receive information (through email or regular mail) on how to download, log in and use the video and chat functions in the STAAR app. Subsequently, potential participants will be invited to take part in a video call via the STAAR app including a structured interview regarding the persons experience and ability to download, install, and use different features of the STAAR app (e.g., chat and responding to a questionnaire). During this second interview, potential participants will also be instructed to describe and show where in their home they intend to perform the home-based exercises (if allocated to experimental group) and report on potential barriers and safety aspects related to exercising at home. The video interview will focus primarily on cognitive assessment of potential participants ability to 1) follow instructions, 2) maintain attention during the interview, 3) demonstrate insight into own abilities and limitations, and 4) show insight into safety aspects related to exercising in the home environment. Based on the two-step screening process, alongside a doctor’s certificate confirming diagnosis and ability to engage in moderate to vigorous physical activity, a decision on study inclusion will be made.

### Baseline characteristics

Self-reported demographics (age, sex, comorbidities, level of education, employment status and living situation), date of stroke/TIA, number of previous strokes/TIA, use of mobility device (e.g., walking stick, rollator or wheelchair) and falls history during the previous 6-months will be collected at baseline using digital questionnaires administered through the STAAR app. In addition, self-perceived impact of stroke and lifestyle habits (tobacco, alcohol, physical activity and diet) will be assessed using electronic versions of the Stroke Impact Scale [39] and the screening survey by National Board of Health and Welfare, respectively.

### Randomisation

Following screening and baseline assessment, eligible participants will be randomised to either 1) an experimental group receiving the i-REBOUND programme or 2) a control group receiving the standard approach for physical activity promotion used in Sweden known as ‘Physical Activity on Prescription’ [16]. The randomisation will be performed in blocks of 2 and will be stratified according to mobility status (with/without walking aid) and geographical region (urban/rural areas). The randomisation schedule will be prepared by an independent researcher, and coded into a trial database, ensuring allocation concealment. The researcher responsible for data management and analysis will be blinded to group allocation.

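### Fixed blocks of 2 let anyone who knows the previous allocation in a stratum know the second of each pair, so the protocol's assurance of allocation concealment is not supported for those allocations

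*Protocol article*

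**What the plan says.** The protocol article (Randomisation) fixes one block size and two stratification factors: "The randomisation will be performed in blocks of 2 and will be stratified according to mobility status (with/without walking aid) and geographical region". The factors are binary ("mobility status (with/without walking aid) and geographical region (urban/rural areas"), giving four strata. An independent researcher prepares the schedule, which is "coded into a trial database, ensuring allocation concealment". Randomisation follows screening and baseline assessment. The only person described as blinded is the researcher responsible for data management and analysis.

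On who enrols, Study procedures says: "Screening for eligibility of study participants will be performed in two steps by members of the research team". The second step is a structured video interview that assesses instruction-following, attention, insight and awareness of safety at home. The same section says the digital clinic is used by the physiotherapists of both arms and "by the research team to coordinate the trial and to collect data on feasibility, acceptability and clinical outcomes". The Interventions section has the research team supporting the physiotherapists in regular meetings held separately by arm. Ethics and dissemination has a research team member contacting participants who are disappointed with control allocation.

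**The concern.** Concealment means that whoever decides on inclusion cannot foresee the next assignment. Hiding the list achieves this only if the next entry cannot be deduced from earlier ones. In a pair with one place per arm, the second entry can be deduced once the first is known, and here the first becomes visible through treatment: one arm receives supervised exercise by video, the other only counselling and scheduled follow-ups.

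A screener who knew the next arm could, without intending to, include, postpone or decline a borderline candidate accordingly. The interview asks where the person would exercise if allocated to the experimental arm, so such a screener might even have a protective motive. At stake are the between-arm comparisons of blood pressure, physical activity and the questionnaire outcomes, and possibly the recruitment proportions, drop-out and adverse-event counts that are to inform the full-scale trial.

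**Working it through.** The protocol states no figure for predictability, so there is none to reproduce. It can be calculated directly.

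**Inputs from the protocol article**
- Sample size 120 and 1:1 allocation (Abstract, Methods)
- Block size 2, with no variation stated (Randomisation)
- Strata: 2 × 2 = 4 (Randomisation)

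**Assumed:** the stratum sizes, which are not given. Two cases were used: 30/30/30/30 and 41/35/27/17.

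**Step 1. Allocations fixed by the previous one.** In each stratum of size n, the number is floor(n/2).
- 30/30/30/30: 4 × 15 = 60 of 120 (50%).
- 41/35/27/17: 20 + 17 + 13 + 8 = 58 of 120 (48%).

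The total is 120, so the number of odd strata is 0, 2 or 4. The count is then (120 − 0)/2 = 60, (120 − 2)/2 = 59 or (120 − 4)/2 = 58. The range 58 to 60 therefore covers every possible split.

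**Step 2. Best-guess rate.** The first of a pair is guessed with probability 0.5 and the second with probability 1.
- 60 fixed: (60 × 1 + 60 × 0.5)/120 = 90/120 = 75%.
- 58 fixed: (58 × 1 + 62 × 0.5)/120 = 89/120 = 74%.

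Under full unpredictability the rate is 50%.

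**Step 3. Alternatives.** Values for fixed blocks come from enumerating all balanced sequences in a complete block. Values for mixed blocks come from simulation with both sets of stratum sizes, for an observer who does not know the order of block sizes.

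| Scheme | Certain in advance | Guessed correctly |
|---|---|---|
| Fixed 2 | 50% | 75% |
| Fixed 4, size known | 33% | 71% |
| Fixed 6, size known | 25% | 68% |
| Mixed 4 and 6, order undisclosed | about 6% | 68–69% |

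The 6% applies to an observer who knows that the sizes are 4 and 6 but not their order. If the sizes are also withheld, the observer can be certain even less often.

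**Step 4. Balance.** An incomplete block of 2 leaves at most 1 extra participant in one arm of a stratum, and an incomplete block of 6 at most 3. In simulation, the mean overall difference between arms stayed below 2 of 120 for every scheme examined.

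**Step 5. Is the stratum known beforehand?** Ambulation status is assessed at the telephone screen (Study procedures). Urban or rural residence is not said to be recorded then. However, the blood pressure monitor is sent before baseline measurement and activity monitors are posted at each assessment (Clinical outcomes), so an address is presumably held before randomisation.

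**The case against.** The strongest reply is that the exposure is conditional. A reader might infer that the whole research team sees every assignment and that concealment has therefore failed outright. The article does not support that. No section says that those who screen see earlier allocations by stratum, and at least one researcher is stated to be blinded. Separation of roles may be set out in a fuller protocol. The independently prepared, database-held list does conceal itself and the first allocation of every pair. This part of the reply stands.

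Timing also matters. Randomisation comes after baseline, which includes 7-day activity and blood pressure recording. If someone else in the stratum is randomised in that interval, the arm foreseen at the inclusion decision may no longer be the next one. The 58 to 60 is therefore an upper bound at inclusion. The timing and order of randomisation could still be steered.

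Screening is not purely discretionary: a doctor's certificate, a questionnaire-based activity threshold and a structured interview all apply. Judgement on attention, insight and safety nevertheless remains.

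Finally, feasibility outcomes are mainly descriptive and effects are labelled preliminary. The mixed model includes baseline as a time level, so it can account for imbalance in measured baseline values, though not in unmeasured traits such as insight or motivation. This lowers the severity. It does not justify the assurance given in the Randomisation section.

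**Conclusion.** The point holds in limited form. With fixed blocks of 2, 58 to 60 of 120 allocations (48–50%) are fully determined for anyone who knows the block size, which is published, and the previous allocation in that stratum. Such a person guesses 74–75% correctly. The hidden list protects only the first of each pair, so the unqualified statement on concealment goes too far.

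Whether a screener actually has that knowledge is an inference. It rests on the distinguishable arms, the shared digital clinic, the arm-specific meetings, the contact with disappointed control participants and the absence of any described separation of roles. Selection bias is therefore possible, not demonstrated. Given the trial's feasibility purpose and preliminary effect estimates, this is something that should be fixed and not a fatal flaw.

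**What to change.** 1. For the remaining allocations, have the independent researcher use randomly permuted blocks of varying size (for example 4 and 6) within the same four strata. Keep the sizes and their order out of documents available to recruiting staff.
2. Record the inclusion decision and baseline data irrevocably before each allocation is released. The protocol already has this order; the addition is that the record cannot then be changed.
3. Where existing staffing allows, keep screeners unaware of earlier allocations.
4. Qualify the concealment sentence in the Randomisation section. For participants already randomised in blocks of 2, report predictability as a limitation. This applies even if recruitment is too advanced to change the list.

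The cost is a new list and a short protocol amendment, with a possible imbalance at the end of recruitment of at most 3 per stratum instead of 1. The benefit is partial: correct guessing falls only from 75% to about 69%. The main gain is that near-certainty about the next arm largely disappears.
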